### **6.2.1.5 Suspected Adverse Reactions/Adverse Reactions**

The following AEs will be considered as ARs:

- All AEs occurring within 1-month post-PR006A administration procedure
- All AEs assessed as at least possibly related to the injection procedure or to investigational product treatment by the Investigator or Sponsor
- All AEs for which the Investigator's causality assessment is missing or indeterminate

### **6.2.1.6 Reporting Serious Adverse Events**

Any AE that meets SAE criteria ([Section 6.2.1.2](#)) from the time of signing the consent form until completion of the 4-year extended follow-up period (as detailed in [Section 6.2.1.3](#)) must be reported in the eCRF within 24 hours after the time that study site personnel first learn about the event. After the 5-year reporting window, any SAE that the Investigator considers related to investigational product must be reported to the contract research organization (CRO) or the Sponsor/designee.

Study site personnel should complete the AE eCRF using electronic data capture (EDC), designating the event as serious. If EDC is unavailable, study site personnel should complete an SAE form and report the SAE by calling the SAE Hotline or faxing the report using the information provided in the Contact List.

### **6.2.1.7 Expedited Reporting Requirements**

All SAEs that occur during the SAE reporting period must be reported by entering the information into the study specific SAE report form and submitting to the CRO within 24 hours of the site becoming aware of the event. Investigators should not wait to collect information that fully documents the event before notifying Prevail of an SAE. Prevail may be required to report certain SAEs to regulatory authorities within 7 calendar days of being notified about the event; therefore, it is important that Investigators submit any information requested by Prevail as soon as it becomes available. Additional follow-up information, if required or available, should all be submitted to Prevail and the CRO within 24 hours of receipt in the study-specific SAE report form.

### **6.2.1.8 Suspected Unexpected Serious Adverse Reactions**

A suspected unexpected serious AR (SUSAR) is defined as any suspected AR to study treatment that is both serious and unexpected.

The event(s) must meet all of the following criteria:

- Suspected AR
- Serious
- Unexpected
- Assessed as at least possibly related to study treatment or if Investigator's causality assessment is missing or indeterminate

The Sponsor will promptly evaluate all SUSARs against cumulative product experience to identify and expeditiously communicate possible new safety findings to Investigators, IRBs/IECs, and applicable health authorities based on applicable legislation.

To determine reporting requirements for single AE cases, the Sponsor will assess the expectedness of these events using the IB.

Reporting requirements will also be based on the Investigator's assessment of causality and seriousness, with allowance for upgrading by the Sponsor as needed.

### **6.2.1.9 Assessment of Severity**

The severity of all AEs should be graded according to the Common Terminology Criteria for Adverse Events (CTCAE) Version 5.0. These criteria can be found at [https://ctep.cancer.gov/protocolDevelopment/electronic\\_applications/docs/CTCAE\\_v5\\_Quick\\_Reference\\_8.5x11.pdf#search=%22CTCAE%22](https://ctep.cancer.gov/protocolDevelopment/electronic_applications/docs/CTCAE_v5_Quick_Reference_8.5x11.pdf#search=%22CTCAE%22). For those AE terms not listed in the CTCAE, the following grading system should be used:

- CTCAE Grade 1: Mild; asymptomatic or mild symptoms; clinical or diagnostic observations only; intervention not indicated
- CTCAE Grade 2: Moderate; minimal local or noninvasive intervention indicated; limiting age appropriate instrumental activities of daily living

- CTCAE Grade 3: Severe or medically significant but not immediately life-threatening; hospitalization or prolongation of hospitalization indicated; disabling; limiting self-care activities of daily living
- CTCAE Grade 4: Life-threatening consequences; urgent intervention indicated
- CTCAE Grade 5: Death related to the AE.

Changes in the severity of an AE should be documented to allow an assessment of the duration of the event at each level of intensity to be performed. Adverse events characterized as intermittent do not require documentation of onset and duration of each episode.

#### **6.2.1.10 Assessment of Causality**

The Investigator's assessment of an AE's relationship to investigational product is part of the documentation process, but it is not a factor in determining what is or is not reported in the study. If there is any doubt as to whether a clinical observation is an AE, the event should be reported.

The relationship or association of the investigational product or the ICM administration of the investigational product in causing or contributing to the AE will be characterized using the following classification and criteria:

- **No** (unrelated, not related, unlikely to be related) – The time course between the administration of investigational product and the occurrence or worsening of the AE rules out a causal relationship and another cause (concomitant drugs, therapies, complications, etc.) is suspected.
- **Yes** (possibly, probably, or definitely related) – The time course between the administration of the investigational product and the occurrence or worsening of the AE is consistent with a causal relationship should be considered at least possibly related to investigational product or investigational product administration procedure. This is defined as all AEs that begin during or within 1 month following investigational product administration, plus all AEs regarded by the Investigator or Sponsor as at least possibly related to investigational product or investigational product administration procedure, plus all AEs for which the Investigator's causality assessment is missing or indeterminate.

### **6.2.1.11 Follow-Up of Patients Reporting Adverse Events**

All AEs must be reported in detail on the appropriate page in the eCRF and followed to satisfactory resolution, until the Investigator deems the event to be chronic or not clinically significant, or until the patient is considered to be stable.

## **6.2.2 Risk Mitigation Plan**

PR006A is not approved and clinical development is ongoing. The anticipated important safety risks for PR006A are provided in this section. Several measures will be taken to ensure the safety of patients participating in this study; patients with anticipated risks from study procedures are excluded while determining eligibility. Patients will undergo frequent safety monitoring during the study, including assessment of the nature, frequency, and severity of AEs. Patient safety will also be reviewed by an iDMC who will provide recommendations regarding further dosing. In addition, guidelines to manage AEs are provided in ensuing sections.

### **6.2.2.1 Mitigation of Risks Associated with Lumbar Puncture**

Lumbar punctures performed for obtaining CSF for biomarker and safety assessments will be performed with care to minimize AEs. Cerebrospinal fluid leakage is more likely with large bore needles. The use of narrow-gauge needles and adherence to the guidelines in the study Procedure Manual will be implemented. Lumbar punctures may be performed under fluoroscopy guidance if this is requested by the local standard of care and/or if clinically indicated as per the Investigator's judgment.

Post-LP headaches sometimes occur within days after the procedure. If a post-LP headache develops, the patient should be encouraged to sit or preferably lie down in a comfortable position. Supportive treatment may include rehydration and consumption of caffeinated drinks, over-the-counter analgesics, and antiemetics. If these conservative measures fail, more specific measures may be indicated including use of a blood patch.

Post-LP spinal hematoma is a very rare but potentially serious complication that can present as persistent back pain, radicular pain, new sensory or motor symptoms, sphincter disturbance, or meningism. Prompt MRI of the lumbar spine should be performed if suspicion of spinal hematoma arises. Patients with susceptibility to bleeding are at an increased risk of spinal hematoma; as such, patients with coagulation abnormalities are

excluded from the study. Patients on blood thinners within the 2 weeks prior to Screening or who are anticipated to require initiation of blood thinners during the study are also excluded, as are patients who are on antiplatelet medications (prophylactic aspirin, clopidogrel) and are medically unable to temporarily halt the use of these drugs from at least 7 days prior to and at least 48 hours after intracisternal injection and LP. Management of spinal hematomas should be in consultation with neurosurgical professionals.

Meningitis is a rare potential risk of LP. Patients may present with headache, meningism, photophobia, neck stiffness, and pyrexia. If meningitis is suspected, a thorough meningitis workup, consultation with appropriate specialists, and prompt use of antibiotics should be considered urgently.

#### **6.2.2.2 Risks Associated with the Use of Immunosuppressants**

One loading dose of 6 mg oral sirolimus will be administered at Day -1, as well as a single dose of 1 g IV methylprednisone at Day 0. A concomitant maintenance dose of 2 mg/day sirolimus will be administered orally for 90 days starting at Day 0 which will then be tapered over the ensuing 15 to 30 days. The maintenance dose is administered to achieve trough sirolimus concentration of 4 ng/mL (range 2 to 8 ng/mL). One day after treatment with PR006A, patients will start prednisone 30 mg orally for 14 days, followed by a 7-day taper. At the Investigator's discretion, adjustments of dose and duration are permitted.

Corticosteroids are administered for prophylactic suppression of inflammatory responses and to improve viral transduction. Despite the beneficial effects of prednisone and sirolimus in the prevention and management of potential liver enzyme abnormalities, systemic immunosuppressants in this dose range can produce a variety of AEs ranging from mild irritability to life-threatening or even fatal biochemical effects including but not limited to impaired wound healing, interstitial lung disease, hyperglycemia, hypertension, lymphomas/malignancies, hyperlipidemia, decline in renal function, proteinuria, embryo-fetal toxicity, and male fertility. While patients will be excluded if they are at increased risk of AEs, if corticosteroid side effects emerge, corticosteroids will be stopped or tapered as medically indicated. Glucose level checks, HbA1c, fructosamine, blood pressure, body weight, cholesterol, urine protein, lipids, red blood cell counts, neutrophil counts, protein glucose, CSF cell counts, CSF protein levels, CSF glucose levels, sirolimus trough concentrations, BMI, waist circumference, and psychosis incidence/aggravation will be monitored at study visits occurring during corticosteroid usage and after prednisone

discontinuation. The iDMC will assess safety variables as listed for the primary safety endpoints ([Section 2](#)) and as detailed in [Section 11.1.1](#). Patients must have evidence of a negative MTB test and pneumococcal pneumonia and shingles vaccination coverage (within 10 years prior to Screening; allowed during Screening Period but at least 4 weeks prior to sirolimus loading dose) in order to initiate prednisone or sirolimus. Additionally, if medically indicated and as per local standard of care, Principal Investigators may consider performing EBV, CMV, and JC virus testing as well anti-viral (e.g., valganciclovir) and/or antibacterial (e.g., low-dose Bactrim) prophylaxis during sirolimus course.

If steroid or sirolimus side effects emerge, these drugs will be stopped or tapered as medically indicated. Details regarding additional monitoring for corticosteroid and sirolimus-related events are provided in [Section 5.5.1.3](#)

If clinically indicated and/or as per local practice, concomitant gastroprotective prophylactic medication, as well as potassium and/or calcium/vitamin D3 and bisphosphonate supplementation, may be initiated. Specifically, for patients with pre-existing osteoporosis (without history of vertebral fracture in the past year) or history of fragility fracture, the Investigator should consider prescribing appropriate therapy intended to prevent/attenuate glucocorticoid-induced osteoporosis starting at the time of initiation of prednisone administration. The same consideration to provide therapy to prevent/attenuate glucocorticoid induced osteoporosis should be given to patients whose prednisone treatment may be extended beyond 6 weeks. A dual-energy x-ray absorptiometry (DEXA) scan will be performed at Screening and will be repeated at Month 12 for patients with baseline osteopenia or osteoporosis ([Section 6.16](#)). For patients receiving prednisone for more than 3 months, HbA1c will be measured at the end of prednisone therapy.

Continued participation in the study will not be affected if the patient or Investigator finds corticosteroid administration to be intolerable or the patient develops clinically significant AEs requiring early prednisone or sirolimus discontinuation.

The following TEAEs, which may be associated with immunosuppressant regimen (see above text), should be explicitly monitored:

- Peptic ulcer disease
- Erosive gastritis

- Osteoporosis
- Increase in body weight  $\geq 5\%$  from baseline
- BMI  $>25$  or  $>30$
- Increase in waist circumference  $\geq 15\%$  from baseline
- Grade  $\geq 3$  infections
- Incidence or aggravation of psychosis
- Hyperlipidemia/hypercholesterolemia
- Renal insufficiency
- Opportunistic infections (including progressive multifocal leukoencephalopathy (PML) and BK virus-associated nephropathy)
- Proteinuria
- Anemia
- Severe neutropenia

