## **5.5 Investigational Product Administration**

### **5.5.1 Immunosuppressant Administration**

#### **5.5.1.1 Corticosteroid Administration**

Subjects will receive a loading dose of methylprednisolone 1 g IV pulse on Day 0. Prednisone at a dose of 30 mg/day will be given orally as concomitant medication from Day 1 for 14 days, which will be then tapered over the ensuing 7 days. At the Investigator's discretion, higher doses or a longer taper of corticosteroids may be used.

Mitigation of risks associated with use of corticosteroids, including monitoring for AEs that may be related to corticosteroid use are described in [Section 6.2.2.2](#).

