## **6.13 Height, Weight, Body Mass Index, and Waist Circumference**

Height will be measured at Screening only. Weight and waist circumference will be measured and BMI calculated during Screening, Month 2, and every 3 months post-administration of PR006A through Month 12. New or worsened clinically significant abnormal findings will be recorded as AEs/SAEs.

Waist circumference measurement should be made at the approximate midpoint between the lower margin of the last palpable rib and the top of the iliac crest. The tape should be snug around the body, but not pulled so tight that it is constricting. The mean of 2 measurements will be recorded.

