| Inclusion/exclusion criteria                              | X                                 | X                           |                |                |    |    |    |       |         |                 |   |   |                        |             |
| Medical and family history and demographics               | X                                 |                             |                |                |    |    |    |       |         |                 |   |   |                        |             |
| Inpatient stay                                            |                                   | X c              | X d | X e |    |    |    |       |         |                 |   |   |                        |             |
| Clinical Assessments and Procedures                       |                                   |                             |                |                |    |    |    |       |         |                 |   |   |                        |             |
| Height, weight, BMI, and waist circumference j | X                                 |                             |                |                |    |    |    |       | X       | X               | X | X | X                      | X           |
| Physical examination k                         | X                                 |                             | X              |                |    | X  |    |       | X       | X               | X |   | X                      | X           |
| Vital signs l                                  | X                                 | X                           | X              | X              | X  | X  | X  | X     | X       | X               | X | X | X                      | X           |
| Prior and concomitant medication review                   | X                                 | X                           | X              | X              | X  | X  | X  | X     | X       | X               | X | X | X                      | X           |
| Adverse events                                            | X m                    | X m              | X              | X              | X  | X  | X  | X     | X       | X               | X | X | X                      | X           |

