| Visit Window in Days                                                         |                                   |                             |                |                | ±1 | ±2 | ±2 | ±7 | +
14 | ±7 g |   |   |                        |             |  |
| Laboratory Assessments                                                       |                                   |                             |                |                |    |    |    |    |         |                 |   |   |                        |             |  |
| HBsAg, HCVAb, and HIV                                                        | X                                 |                             |                |                |    |    |    |    |         |                 |   |   |                        |             |  |
| Hematology, blood chemistry (incl lipid panel and coagulation f ) | X                                 | X                           |                |                | X  | X  | X  | X  | X       | X               | X | X | X                      | X           |  |
| HbA1c e,s                                                         | X                                 | X                           |                |                |    |    |    |    | X       | X               |   |   |                        | X           |  |
| Fructosamine f                                                    |                                   | X                           |                |                | X  |    |    |    |         |                 |   |   |                        | X           |  |
| Urinalysis                                                                   | X                                 | X                           |                |                | X  | X  | X  | X  | X       | X               | X | X | X                      | X           |  |
| Urine biomarker                                                              | X                                 |                             |                |                |    |    |    | X  | X       | X               | X | X | X                      | X           |  |

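### Section 6.2.2.2 says weight, BMI, waist, HbA1c, fructosamine and CSF are monitored at visits during steroid use, but the schedule mostly does not deliver this, so a weight or waist gain that reverses before Month 2 cannot be counted

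*Protocol*

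**What the plan says.** Section 6.2.2.2 of the protocol gives a list that opens with "Glucose level checks, HbA1c, fructosamine, blood pressure, body weight, cholesterol, urine protein, lipids, red blood cell counts, neutrophil counts" and goes on to CSF cell counts, protein and glucose, sirolimus trough, BMI and waist. It closes: "waist circumference, and psychosis incidence/aggravation will be monitored at study visits occurring during corticosteroid usage and after prednisone" discontinuation. Nothing in the sentence limits it to scheduled visits.

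The steroid course is set in Section 5.5.1.1: "Subjects will receive a loading dose of methylprednisolone 1 g IV pulse on Day 0", then oral prednisone "from Day 1 for 14 days, which will be then tapered over the ensuing 7 days". The same section lets the investigator raise the dose or lengthen the taper.

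For body measurements, Section 6.13 has weight and waist measured and "BMI calculated during Screening, Month 2, and every 3 months post-administration of PR006A through Month 12". The Table 13-1 row "Height, weight, BMI, and waist circumference" agrees with this.

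The primary safety endpoint (Section 2, Section 7.1.1 and the synopsis) names a weight increase of at least 5%, BMI above 25 or above 30, and a waist increase of at least 15%. Section 6.2.2.2 puts the same three among the events to be explicitly monitored because they may be associated with the immunosuppressant regimen.

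**The concern.** The risk-mitigation text describes monitoring that the schedule does not contain. Sites work from the schedule, so a reader of Section 6.2.2.2, such as an ethics committee or the iDMC, would believe that more is measured on steroids than is.

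For most items on the list this is only a mismatch of wording. For weight, BMI and waist it goes further. These are threshold events within the primary safety endpoint, and they can be established only with a scale and a tape. If nothing is measured between Screening and Month 2, an event that arises on steroids and has gone by Month 2 leaves no record. The reported incidence would not show whether such events occurred.

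**Working it through.** The plan gives no figure to reproduce. The check sets the steroid window against the rows of Table 13-1.

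**Window.** The IV pulse is on Day 0. Table 13-1 footnote c allows it on Day -1, but after that day's blood samples, so the Day -1 HbA1c and fructosamine remain pre-steroid values. Prednisone runs Days 1 to 14 and the taper Days 15 to 21 (14 + 7 = 21). Visits in the window are Days 0, 1, 7, 14 and 21, five in all.

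**Schedule, main study period (unscheduled visits left out).**

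| Item | Scheduled at | Steroid visits covered | After prednisone ends |
|---|---|---|---|
| Weight, BMI, waist | Screening; Months 2, 3, 6, 9, 12 | 0 of 5 | Yes, from Month 2 |
| HbA1c | Screening; Day -1; Months 2, 3 | 0 of 5 | Yes, Months 2 and 3 |
| Fructosamine | Day -1; Day 7 | 1 of 5 | None |
| CSF by lumbar puncture | Screening; Months 2, 12 | 0 of 5 | Yes, Months 2 and 12 |
| CSF from the cisterna magna | Day 0 | 1 of 5, before injection | Not applicable |
| Blood chemistry | Screening; Day -1; Days 7, 14, 21; Months 1, 2, 3, 6, 9, 12 | 3 of 5 | Yes |
| Urinalysis | Same visits as chemistry | 3 of 5 | Yes |

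Section 6.5 places glucose in both the chemistry panel and the urinalysis, and requires fasting chemistry from Screening to the end of the corticosteroid taper. Fasting serum glucose and urine glucose are therefore obtained at Days 7, 14 and 21.

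**Gap to the first post-dose weight.** The Month 2 visit has a window of +14 days. Gap = Month 2 day − 21.

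- 30-day months: 60 − 21 = 39 days; at the end of the window, 74 − 21 = 53 days.
- 28-day months: 56 − 21 = 35 days; 70 − 21 = 49 days.
- 30.4-day months: 60.8 − 21 = 39.8 days; 74.8 − 21 = 53.8 days.

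Across these assumptions the gap is about 35 to 54 days.

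**Longer taper.** Section 5.5.1.3 mentions a taper extended by another 4 weeks. Added to Day 21 this ends at Day 49 (21 + 28), still before Month 2. The Month 1 visit carries no mark for weight.

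**The case against.** The strongest reply is that Section 6.2.2.2 is risk narrative and need not mean every item at every visit. Sections 6 and 6.5 make Tables 13-1 and 13-2 the operative schedule, Section 6.13 agrees with the table on weight, BMI and waist, and all of the disputed items except fructosamine are measured after prednisone ends. On this view one corrected sentence is enough. It stands in part: the text is the outlier, and sites have a clear schedule. But the sentence joins the two periods with an *and*, and no loose reading puts a weight measurement in the first. Correcting only the sentence would remove the contradiction and leave the measurement gap.

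Three stronger inferences are tempting, and the protocol does not support them.

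- *Steroid-phase glycemic effects are missed.* They are not. Fasting glucose and urine glucose are scheduled three times during the oral course and taper, with fructosamine at Day 7. The mismatch concerns HbA1c and fructosamine as assays.
- *No CSF is obtained during steroid use.* Cisternal CSF is collected on Day 0, the default day of the IV pulse. It precedes the PR006A injection, and the footnote to that row is not readable in the public text, so its assays cannot be confirmed. What can be said is that no CSF is scheduled after it until Month 2.
- *The reported incidence of weight and waist events is bound to be too low.* That holds only for gains that reverse before Month 2, and no document gives a time course showing how often this happens. Sirolimus continues for 90 days with a further 15 to 30 days of taper, so the Month 2 weight, and the Month 3 weight too, fall within the wider immunosuppressant regimen to which Section 6.2.2.2 ties these events.

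Adverse events are reviewed at every visit, a physical examination is marked at Day 14, and weight is marked for unscheduled visits. These may pick up a conspicuous gain, but they do not systematically measure a percentage threshold.

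**Conclusion.** The contradiction is real. Under the default course, weight, BMI, waist and HbA1c have no scheduled measurement at Days 0 to 21, and CSF has none between the pre-injection sample on Day 0 and Month 2. Fructosamine is measured once on steroids and never on schedule after prednisone ends, so for that assay both halves of the statement fail.

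The practical consequence is narrow. A weight, BMI or waist event that arises on steroids and reverses before about Day 60 to 74 cannot be counted in the primary safety endpoint; one that persists is captured at Month 2. How many events this would hide cannot be estimated from the protocol.

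This rests on the default steroid course, 30-day months, and the column positions in the published table. Section 6.13 confirms those positions independently for weight, BMI and waist. The point is worth correcting because a named primary safety component is affected and the remedy is cheap. It does not put the trial's validity in doubt.

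**What to change.** Reconcile Section 6.2.2.2 with Section 6.13 and Table 13-1.

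1. In Table 13-1 and Section 6.13, add weight (with calculated BMI) and waist at existing early visits, for example Days 14 and 21 and Month 1. For 15 planned patients this is 3 × 15 = 45 extra measurement occasions with a scale and tape, and no new visits.
2. In Section 6.2.2.2, limit the statement on HbA1c, fructosamine and CSF to the visits at which each is scheduled. No lumbar puncture is added.
3. Optionally, run fructosamine on chemistry blood already drawn after Day 7. At Days 14 and 21 and Month 1 that would be 3 assays per patient. Fasting glucose already covers these visits, so this is a choice and not a need.

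The cost is a few schedule marks, one revised sentence and the measurements in item 1. No treatment rule changes.
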